**APPENDIX 6 – ALS ASSESSMENT QUESTIONNAIRE (ALSAQ-40)**

**Please visit the following website for details about the ALSAQ-40:**

**<https://innovation.ox.ac.uk/outcome-measures/amyotrophic-lateral-sclerosis-assessment-questionnaire-alsaq/>**

The research commercialisation office of the University of Oxford, previously called **Isis Innovation**, has been renamed **Oxford University Innovation**

All documents and other materials will be updated accordingly. In the meantime the remaining content of this Isis Innovation document is still valid.

URLs beginning [www.isis-innovation.com/](http://www.isis-innovation.com/)... are automatically redirected to our new domain, [www.innovation.ox.ac.uk/](http://www.innovation.ox.ac.uk/)...

Phone numbers and email addresses for individual members of staff are unchanged

Email: [[contact]](mailto:[contact])

---

**APPENDIX 7 – EQUATION FOR ESTIMATED GLOMERULAR FILTRATION RATE****COCKCROFT-GAULT**

Creatinine clearance (estimated GFR) =  $\frac{[(140 - \text{age in years}) \times (\text{wt in kg})] \times 1.23}{(\text{serum creatinine in micromol/l})}$

---

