## 4. ELIGIBILITY

### 4.1 Main Eligibility criteria

#### Inclusion Criteria:

1. Patients  $\geq 18$  years and who have provided written informed consent to participate in the study
2. Prior to trial entry patients will have a *definite* diagnosis of ALS according to El Escorial Criteria (Appendix 10). All patients will demonstrate either:
  - **presence of Upper Motor Neuron (UMN)** (increased tone, brisk reflexes) **as well as Lower Motor Neuron (LMN)** (weakness, wasting and fasciculation) **signs in the bulbar region and at least two of the other spinal regions** (cervical, thoracic or lumbosacral)
  - or
  - **presence of UMN and LMN signs in all three spinal regions** (cervical, thoracic or lumbosacral)
3. Electrophysiological tests (Electromyography (EMG) / Nerve Conduction Study (NCS)) that supports the diagnosis of Motor Neurone Disease (MND) and to exclude mimic disorders
4. Forced Vital Capacity (FVC)  $\geq 50\%$  of predicted value for gender, height and age at screening and/or a mean Sniff Nasal Inspiratory Pressure (SNIP)  $\geq 50\%$  of predicted value for age
5. Adequate haematological function (Hb  $\geq 10\text{g/dl}$  absolute neutrophil count  $\geq 1.5 \times 10^9/\text{L}$  and a platelet count  $\geq 60 \times 10^9/\text{L}$ )
6. International Normalised Ratio (INR)  $\leq 1.5$ , Activated Partial Thromboplastin Time (aPTT)  $\leq 40$  seconds, Prothrombin Time (PT)  $\leq 13.5$  seconds
7. Patient willing and able to comply with schedule visits, treatment plan and other study procedures.
8. Patients taking Riluzole must have discontinued treatment  $\geq 28$  days prior to study entry (and following consent to take part in the study)
9. Women Of Child Bearing Potential (WOCBP) who agree to use highly effective means of contraception (as defined in the Heads of Medicines Agencies\_Clinical Trials Facilitation Group (HMA\_CTFG) guideline (see Appendix 8) and in combination with a barrier contraception method (condom, diaphragm or cap) for the entirety of the study

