### 7.3 Assessments

#### 7.3.1 Blood chemistry and Haematology

The following blood tests will be performed at each visit. All safety assessments will be done in local laboratories at the investigative site.

| Biochemistry      | Blood test                                                                                                                                                                                                                                                                                                                           |
|-------------------|--------------------------------------------------------------------------------------------------------------------------------------------------------------------------------------------------------------------------------------------------------------------------------------------------------------------------------------|
| U&Es              | Sodium
Potassium
Urea
Creatinine
*Estimated Glomerular Filtration Rate (eGFR) (calculated by Cockcroft-Gault equation or alternative as per institutional practice – Appendix 6)                                                                                                                                         |
| LFTs              | Albumin
Aspartate transaminase (AST)
Alanine Transaminase (ALT)
Alkaline Phosphatase (ALP)
Bilirubin (direct and indirect if total is $\geq 30$ )
Gamma Glutamyl Transpeptidase (GGT)                                                                                                                                 |
| Other             | Serum Creatine Kinase-MB (CK-MB)
Troponin I (not tested after treatment week 24)
C-reactive protein (CRP)
Glucose
Calcium
Thyroid Stimulating Hormone (TSH) (not tested after treatment week 24)
Free Thyroxine (Free T4) (not tested after treatment week 24)
Immunoglobulin G (IgG)
Immunoglobulin M (IgM) |
| Haematology       | Blood test                                                                                                                                                                                                                                                                                                                           |

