### 8.1 Reporting Requirements

#### 8.1.1 Adverse Events

All medical occurrences which meet the definition of an AE (see Appendix 4 for definition) should be reported. Please note this includes abnormal laboratory findings including those that are not clinically significant.

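### Appendix 7 prints Cockcroft-Gault with the constant 1.23 and no sex term, so any woman's eGFR calculated with it as printed is about 18% too high (minor)

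*Protocol*

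**What the plan says.** Appendix 7 of the protocol is headed as the Cockcroft-Gault equation for estimated GFR. It gives a single expression with numerator "140 - \text{age in years}) \times (\text{wt in kg})] \times 1.23" and, as denominator, "serum creatinine in micromol/l". There is no second constant and no multiplier for women.

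Section 7.3.1 lists eGFR within the U&E panel, "calculated by Cockcroft-Gault equation or alternative as per institutional practice – Appendix 6". Appendix 6 is the ALSAQ-40 page; the equation is in Appendix 7. The same section adds: "All safety assessments will be done in local laboratories at the investigative site". Serum urea and creatinine are measured tests in the same panel.

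Women can enter the trial. Inclusion criterion 9 in section 4.1 covers "Women Of Child Bearing Potential (WOCBP) who agree to use highly effective means of contraception", and pregnancy tests appear in the schedules of assessments.

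Section 8.1.1 requires abnormal laboratory results to be reported as adverse events: "Please note this includes abnormal laboratory findings including those that are not clinically significant". Section 8.1.1.1 excludes a pre-existing condition unless it worsens by at least one CTCAE grade. Section 12.2.1.1 breaks the event counts down by grade.

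**The concern.** The appendix names a specific equation but prints a form without a sex term. A site that followed it literally would overstate eGFR in women by a fixed proportion.

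Safety is a primary outcome. U&Es are taken at screening, at every treatment visit in weeks 1 to 10 and at every main-trial follow-up visit, so the equation could be applied many times per patient. With a target of 15 patients, one value placed on the wrong side of a limit shows in a table of laboratory adverse events. The faulty cross-reference adds to the problem, because a reader who follows 7.3.1 arrives at a questionnaire and not at a formula.

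**Working it through.** **Inputs from the protocol**
- Constant 1.23, creatinine in micromol/l, no sex term (Appendix 7).
- Cockcroft-Gault or an institutional alternative (section 7.3.1).

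**Inputs that are assumptions, not in the protocol**
- Unit conversion of 88.4 micromol/l per mg/dl and the divisor 72 of the mg/dl form, used only to identify the printed constant.
- Female factor 0.85, often written as constant 1.04; range 0.80 to 0.90.
- A cut-off of 60 ml/min, for illustration only.

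**1. Which form is printed.** 88.4 / 72 = 1.228, which rounds to 1.23. The printed constant is therefore the unadjusted form, used for men. With the female factor, 1.228 x 0.85 = 1.044, or 1.04 rounded.

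**2. Size of the overstatement in a woman.** Age, weight and creatinine cancel, so the ratio is the same for every woman:
- constant 1.04: 1.23 / 1.04 = 1.183, or +18.3%
- factor 0.85: 1 / 0.85 = 1.176, or +17.6%
- factor 0.90: 1 / 0.90 = 1.111, or +11%
- factor 0.80: 1 / 0.80 = 1.25, or +25%

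**3. Worked example.** Woman aged 60, 60 kg, creatinine 90 micromol/l:
- as printed: (140 - 60) x 60 x 1.23 / 90 = 65.6 ml/min
- with 1.04: (140 - 60) x 60 x 1.04 / 90 = 55.5 ml/min

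**4. Who could be misclassified.** Only women whose printed value lies between a cut-off and about 1.18 times it. For 60 ml/min the upper end is 60 x 1.183 = 71. Equivalently, the sex-adjusted value lies between 60 / 1.183 = 50.7 and 60.

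**5. Direction once baseline counts.** Take a woman whose sex-adjusted eGFR falls from 58 to 50.
- Sex-adjusted: below 60 at both times, so there is no new crossing of that cut-off.
- As printed: 58 x 1.183 = 68.6 and 50 x 1.183 = 59.1, so there is a new crossing.

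The printed form adds an apparent event here, whereas in step 3 it removes one. The proportional change is the same on both scales: (50 - 58) / 58 = -13.8%.

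**6. Which rules use eGFR.** The main and extension eligibility criteria, the patient and trial stopping rules and the outcome measures do not name it. Table 2 on dose modification works by CTCAE grade and does not name it either.

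**The case against.** The strongest reply is that the printed equation may never have been used. Section 7.3.1 allows "calculated by Cockcroft-Gault equation or alternative as per institutional practice", and safety tests run in local laboratories. If the site used an institutional method, or a sex-adjusted Cockcroft-Gault, the error from this source is zero. That stands, and the documents do not show which method was used. The statement that every woman's eGFR is overstated is therefore not supported; it holds only for values calculated as printed.

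Three further readings are tempting and also fail:

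- *Renal impairment in women is missed.* Creatinine and urea do not depend on the equation, and their abnormal values are reportable under section 8.1.1 in their own right.
- *The error always makes ILB look safer for the kidney.* Step 5 of the working shows that an inflated baseline can create a new event, and a constant multiplier leaves each patient's percentage change intact.
- *The institutional alternative lets one patient's visits be computed by different equations.* This is the role of a single centre's own practice (section 12.6), and nothing suggests that the practice changed between visits.

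It can also be said that correcting the formula has no prospective effect. Section 11 puts the last treatment visits in March 2020, and the later remote visit takes no blood. That is right, but values already calculated can still be corrected before they are reported.

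None of this removes the defect itself. The typed formula is complete, it carries the name of a known equation, and under the stated assumption it is wrong for one sex.

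**Conclusion.** The point holds as a minor error in a stated formula. Any woman's eGFR calculated with Appendix 7 as printed is about 18% too high, with a range of 11% to 25%. This rests on a female factor of 0.85, ranged from 0.90 to 0.80, which the protocol does not give.

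The consequence is confined to eGFR-based adverse events, grades or listings for women near a cut-off, and it can go either way when baseline status is taken into account. The number of women affected cannot be stated, because the documents give neither the sex mix nor the method used, and recruitment ended early. No eligibility, extension, stopping or outcome rule depends on it. The wrong appendix number in section 7.3.1 is a separate slip that needs no assumption.

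**What to change.** - **Appendix 7:** give the constant as 1.23 for men and 1.04 for women.
- **Section 7.3.1:** change the cross-reference from Appendix 6 to Appendix 7, and state which equation produced the reported eGFR values. The institutional option need not be removed.
- **Data:** if the printed equation was used, recompute women's eGFR from recorded creatinine, age and weight before any eGFR-based adverse event or listing is tabulated. If another method was used, say so; no recomputation is then needed on this account.

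The cost is two short text corrections and, at most, a recalculation. Creatinine is in the U&E panel, body weight is part of the vital signs, and date of birth is collected at trial entry, so no new patient contact is needed. The downside is that a few eGFR values in women may be reclassified.

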## APPENDIX 8 – HMA CTFG GUIDELINES ON CONTRACEPTION

### Birth control methods which may be considered as highly effective

For the purpose of this guidance, methods that can achieve a failure rate of less than 1% per year when used consistently and correctly are considered as highly effective birth control methods. Such methods include:

- combined (oestrogen and progestogen containing) hormonal contraception associated with inhibition of ovulation
  - o oral
  - o intravaginal
  - o transdermal
- progestogen-only hormonal contraception associated with inhibition of ovulation:
  - o oral
  - o injectable
  - o implantable
- intrauterine device (IUD)
- intrauterine hormone-releasing system (IUS)
- bilateral tubal occlusion
- vasectomised partner
- sexual abstinence

### Acceptable birth control methods which may not be considered as highly effective

Acceptable birth control methods that result in a failure rate of more than 1% per year include:

- progestogen-only oral hormonal contraception, where inhibition of ovulation is not the primary mode of action
- male or female condom with or without spermicide
- cap, diaphragm or sponge with spermicide

### Assessment of pharmacokinetic interaction between the IMP and hormonal Contraceptives and recommendations on the use of hormonal contraceptives

For hormonal contraception methods, caution should be taken to possible interaction with a (Non-biologic) IMP. Interaction with the IMP leading to reduced efficacy of the hormonal contraception method can occur due to e.g. increased metabolism (enzyme induction).

### Birth control methods which are considered unacceptable in clinical trials

Periodic abstinence (calendar, symptothermal, post-ovulation methods), withdrawal (coitus interruptus), spermicides only, and lactational amenorrhoea method (LAM) are not acceptable methods of contraception. Female condom and male condom should not be used together.

---

 Hormonal contraception may be susceptible to interaction with the IMP, which may reduce the efficacy of the contraception method (see Section xx)

 Contraception methods that in the context of this guidance are considered to have low user dependency.

 Vasectomised partner is a highly effective birth control method provided that partner is the sole sexual partner of the WOCBP trial participant and that the vasectomised partner has received medical assessment of the surgical success.

 In the context of this guidance sexual abstinence is considered a highly effective method only if defined as refraining from heterosexual intercourse during the entire period of risk associated with the study treatments. The reliability of sexual abstinence needs to be evaluated in relation to the duration of the clinical trial and the preferred and usual lifestyle of the subject.

 A combination of male condom with either cap, diaphragm or sponge with spermicide (double barrier methods) are also considered acceptable, but not highly effective, birth control methods

[figure not shown]

## **APPENDIX 9 – EL ESCORIAL WORLD FEDERATION OF NEUROLOGY CRITERIA FOR THE DIAGNOSIS OF ALS**

### **Criteria for the diagnosis of Amyotrophic Lateral Sclerosis**

The diagnoses of ALS requires the presence of

- 1) Signs of lower motor neuron (LMN) degeneration by clinical, electrophysiological or neuropathologic examination,
- 2) Signs of upper motor neuron (UMN) degeneration by clinical examination, and
- 3) Progressive spread of signs within a region or to other regions, together with the absence of
- 4) Electrophysiological evidence of other disease processes that might explain the signs of LMN and/or UMN degenerations; and
- 5) Neuroimaging evidence of other disease processes that might explain the observed clinical and electrophysiological signs.

### **Steps in the diagnosis of Amyotrophic Lateral Sclerosis**

The diagnoses of ALS is made possible by

- 1) History, physical and appropriate neurological examinations to ascertain clinical finding which may suggest suspected, possible, probable or definite ALS,
- 2) Electrophysiological examinations to ascertain findings which confirm LMN degeneration in clinically involved regions, identify LMN degeneration in clinically uninvolved regions and exclude other disorders,
- 3) Neuroimaging examinations to ascertain findings which may exclude other disease processes,
- 4) Clinical laboratory examinations, determined by clinical judgment, to ascertain possible ALS-related syndromes,
- 5) Neuropathologic examinations, where appropriate, to ascertain findings which may confirm or exclude sporadic ALS, coexistent sporadic ALS, ALS-related syndromes or ALS variants,
- 6) Repetition of clinical and electrophysiological examinations at least six months apart to ascertain evidence of progression.

### **Clinical features in the diagnosis of ALS**

Patients with signs of LMN degeneration (weakness, atrophy and clinical fasciculation's) and UMN degeneration (spasticity, pathologic reflexes, etc.) may be suspected as having ALS. Careful history,

The ALS Association, [name],  
[contact] / [[contact]](mailto:[contact]) / [www.alsa.org](http://www.alsa.org)

[figure not shown]

physical and neurological examination must search for further clinical evidence of LMN and UMN signs in four regions of the central nervous system.

### **Clinical features required for the diagnosis of ALS**

- 1) Signs of LMN degeneration (weakness, wasting and fasciculation) in one or more of the four regions (bulbar, cervical, thoracic, lumbosacral). LMN findings in a region are without regard to right or left, but are indicative of the level of neuraxis involved. Therefore, spread of weakness, wasting and fasciculation's to another region is more important than spread from right to left or vice-versa.
- 2) Signs of UMN degeneration (increased or clonic tendon reflexes, spasticity, pseudo bulbar features, Hoffmann reflex and extensor plantar response) in one or more of the four regions. These UMN signs are clinically appreciated best in the bulbar, cervical and lumbosacral regions. UMN findings in a region are also without regard to right or left. Once the physical and neurological examinations provide information on the presence or absence of LMN and UMN signs in the four regions (bulbar, cervical, thoracic, lumbosacral) they must be ordered topographically in the manner to determine the certainty of the diagnosis of ALS.
- 3) The topographical location of certain UMN and LMN signs in four regions of the CNS together with progression of these signs determines the certainty of the diagnoses of ALS. Progression is a cardinal feature of the clinical diagnosis of ALS. Progression of signs within a region and progression of signs to involve other regions are crucial to the diagnosis.

Clinical examinations should be repeated at least every six (6) months to assess progression.

Cases which meet the topographical criteria for probable or definite ALS but which lack progression during the twelve (12) month period diagnosis should be designated as possible ALS.

### **Definite ALS**

is defined on clinical grounds alone by the presence of UMN as well as LMN signs in the bulbar region and at least two of the other spinal regions or the presence of UMN and LMN signs in three spinal regions. The important determinants of diagnosis of definite ALS in the absence of electrophysiological, neuroimaging and laboratory examinations are the presence of UMN and LMN signs together in multiple regions.

The ALS Association, [name],  
[contact] / [[contact]](mailto:[contact]) / [www.alsa.org](http://www.alsa.org)

[figure not shown]

### Probable ALS

is defined on clinical grounds alone by UMN and LMN signs in at least two regions. While the regions may be different, some UMN signs must be rostral (above) the LMN signs. Multiple different combinations of UMN and LMN signs may be present in patients with probable ALS.

### Possible ALS

is defined on clinical grounds alone when the UMN and LMN signs are in only one region or UMN signs alone are present in 2 or more regions or LMN signs are rostral to UMN signs (the latter distribution of signs needs to be differentiated from multiple non-ALS processes). Monomelic ALS, progressive bulbar palsy without spinal UMN and/or LMN signs and progressive primary lateral sclerosis without spinal LMN signs and progressive primary lateral sclerosis without spinal LMN signs constitute special cases which may develop LMN or UMN signs to meet the criteria for probable ALS with time or be subsequently confirmed at autopsy by specific LMN and UMN neuropathologic findings.

### Suspected ALS

will manifest only LMN signs in 2 or more regions, although UMN pathology might be demonstrated at autopsy. However, only clinical signs are considered pertinent to this classification at the time of diagnostic evaluation.

### Supportive clinical features

Clinical features that support the diagnosis of ALS include one or more of the following:

- 1) abnormal pulmonary function test not explained by other causes,
- 2) abnormal speech studies not explained by other causes,
- 3) abnormal swallowing studies not explained by other causes,
- 4) abnormal larynx function studies not explained by other causes,
- 5) abnormal isokinetic or isometric strength test in clinically uninvolved muscles,
- 6) abnormal muscle biopsy with evidence of denervation.

### Inconsistent clinical features

Clinical findings inconsistent with the diagnoses of ALS include one or more of the following not explained by physiological changes associated with aging or other disease processes:

The ALS Association, [name],  
[contact] / [[contact]](mailto:[contact]) / [www.alsa.org](http://www.alsa.org)

[figure not shown]

- 1) sensory dysfunction,
- 2) sphincter abnormalities,
- 3) autonomic nervous system dysfunction,
- 4) anterior visual pathway abnormalities,
- 5) movement abnormalities associated with probable Parkinson's disease defined by DATATOP criteria,
- 6) cognitive abnormalities associated with clinical Alzheimer's disease as defined by NINCDS-ADRDA criteria.

If these clinical findings occur, then close attention should be paid to the possible diagnosis of other disease processes.

Lower motor neuron and upper motor neuron signs may occur together with other clinical signs in disease where the pathologic process is not primary motor neuron degeneration.

### Types of ALS

The clinical signs of progressive LMN and UMN degeneration seen in ALS may

- a) occur alone (sporadic ALS),
- b) be present incidentally with other pre-existing disease processes that have not developed in parallel with the ALS (coexistent sporadic ALS),
- c) Occur in association with laboratory-defined or epidemiologically defined abnormalities that are time-linked to the ALS (ALS-related syndromes), or
- d) Occur in association with clinical, genetic or epidemiological features which develop in parallel with the ALS (ALS variants).

The physical and neurological examinations will allow for the clinical diagnosis of ALS to a particular degree of certainty as defined above; however, the history of the disease onset, toxic exposures, past medical history, injuries, family history, geographic location, etc., must be incorporated with the clinical examinations in determining whether the patient may have an ALS related syndrome or an ALS variant.

ALS-related syndromes must meet the clinical, electrophysiological and neuroimaging criteria for possible, probable or definite ALS. ALS-related syndromes have unique laboratory-defined or epidemiologically defined features which are time-linked to the development of the ALS phenotype. If correction of the associated laboratory feature does not result in correction of the ALS phenotype, then the patient with an ALS-related syndrome should be considered in the same way as a patient with sporadic ALS.

The ALS Association, [name],  
[contact] / [[contact]](mailto:[contact]) / [www.alsa.org](http://www.alsa.org)

[figure not shown]

ALS-related syndromes include

- 1) Monoclonal gammopathy (monoclonal gammopathy of unknown significance, Waldenstrom's macroglobulinemia, osteosclerotic myeloma, etc.),
- 2) Dysimmune motor system degeneration (autoimmune; high-titer GMI ganglioside antibody; etc.),
- 3) Nonmalignant endocrine abnormalities (hyperthyroidism, hyperparathyroidism, hypogonadism, etc.),
- 4) Lymphoma (Hodgkin's and non-Hodgkin's lymphoma). Cases of sporadic ALS associated with insulinoma, lung, colon or thyroid cancer are thought not to be casually related,
- 5) Infection (HIV-1, HTLV-I, encephalitis lethargica, varicella-zoster, brucellosis, cat-scratch disease, Creutzfeldt-Jakob disease, syphilis, delayed post-poliomyelitis, etc.),
- 6) Acquired enzyme defects (detoxification enzymes, etc.),
- 7) Exogenous toxins (lead, mercury, arsenic, thallium, cadmium, manganese, aluminum, organic pesticides, lupin seeds, etc.),
- 8) Physical injury (electric shock, radiation therapy, etc.),
- 9) Vascular (vasculitis; ischemic (Dejerine anterior bulbar artery syndrome, etc.),
- 10) Spondylotic myelopathy (painless myelopathy with no sensory signs, stabilization or progression post- surgery).

ALS Variants must meet the clinical, electrophysiological and neuroimaging criteria for possible, probable or definite ALS. The predominant presentation is that seen in sporadic ALS, but includes one or more features such as:

- 1) Familial pattern of inheritance (multiple phenol-types characterized by age of onset; site of onset; length of survival; and presumed type of inheritance.)

Familial ALS variants in genetic linkage studies should be characterized by an established genetic mode of inheritance over at least two generations and at least one clinically definite or autopsy confirmed case and compelling evidence excluding other possible causes. Affected sub pairs occurring in one generation alone may not result from a single gene effect.

Examples:

- a) ALS with defined inheritance and known gene product (hexosaminidase A/B deficiency, superoxide dismutase deficiency)
- b) ALS with defined inheritance and chromosome linkage but no gene product (chromosome 21 associated familial ALS or chromosome 2 associated juvenile familial ALS)

The ALS Association, [name],  
[contact] / [[contact]](mailto:[contact]) / [www.alsa.org](http://www.alsa.org)

[figure not shown]

- c) ALS with defined inheritance and no known linkage or gene product (most cases or familial ALS).
- 2) Geographic clustering (including disorders seen in the Western Pacific, Guam, Kii Peninsula, North Africa, Madras, etc.)
- 3) Extrapyramidal signs (bradykinesia; cogwheel rigidity; tremor; clinically significant onset of supranuclear eye signs (pursuit abnormalities); familial or sporadic)
- 4) Cerebellar degeneration (spinocerebellar abnormalities; familial or sporadic)
- 5) Dementia (progressive cognitive abnormalities; familial or sporadic)
- 6) Autonomic nervous system involvement (clinically significant abnormal cardiovascular reflexes; bowel or bladder control problems; familial or sporadic)
- 7) Objective sensory abnormalities (decreased vibration; sharp-dull discrimination; blunting of cold sensation; familial or sporadic)

